#### Primary objective

3.1.1

A Bayesian design following the work of Spiegelhalter et al. (2004) is proposed to analyze the primary outcome. An a priori distribution for the difference in this percentage of patients in remission after 6 months between both groups has been estimated from the elicitation of 15 clinician's opinions. A structured questionnaire similar to the one used in Parmar, Spiegelhalter, Freedman, and Chart Steering Committee (1994) was used and a short video explaining the study, the Bayesian design and why a priori opinions of clinicians are required were send to the clinicians along with the questionnaires. According to the literature (Spiegelhalter et al., 2004, p. 141), clinicians were as numerous as possible. They were child and adolescent psychiatrists with at least five patients corresponding to the patients included in this study. This group was a mixture of clinicians who had never and who had already referred a patient to TCP. Voluntarily, these clinicians were not experts in TCP to reduce allegiance bias as possible, that is, they have not published on the topic, they were not specialized in TCP, and have not participated regularly (i.e., at least 1 or 2 weeks) to TCP sessions. They were recruited among first‐line care teams who have already referred patients to TCP. A pessimistic a priori distribution was obtained from the experimental a priori distribution, dividing the mean of efficacy by 2 (keeping the same variance).

The final decision concerning treatment effect will be made from the observation of the posterior distribution of the log odds ratio (mixture of two normal distributions weighted by the variances: observed data and a priori distribution), the pessimistic posterior distribution (mixture of observed data and pessimistic a priori distribution), and from the distribution of observed data (uninformative prior). The 95% credible interval of efficacy will be estimated in these three situations.

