### Sample size

2.6

Eighty participants will be enrolled in the study: 40 in experimental group and 40 in control group.

In principle, the sample size in Bayesian designs do not need to be formally justified. Nonetheless, for information and for equivalence with a frequentist design, the following calculation was performed. An a priori distribution was estimated from the elicitation of expert opinions in a pilot study. To limit allegiance bias (associated with the experts' theoretical or treatment preferences), experts were asked to estimate the effect of the care as pessimistically as possible. The following distribution was found for estimates of the difference in the percentage of remission in the two randomized groups: 10%–0%: 0; 0%–10%: 1 expert; 10%–20%: 12 experts; 20%–30%: 4 experts; 30%–40%: 3 experts; 40%–50%: 0. The mean (±SD) of this distribution is 0.195 (±0.0825) and corresponds an a priori of 23 “virtual” subjects per group (the standard deviation 0.0825 being equal to sqrt(*p*[1−*p*]/*n*) where *p* = 0.195 and *n* is the number of virtual subjects per group; Spiegelhalter, Abrams, & Myles, 2004). Added to the 40 “real” subjects (included in this study), the a posteriori overall sample size will therefore be 63 subjects per group. In a frequentist design, a sample size of 63 per group would be sufficient to show a significant 23% difference in efficacy between groups (power = 80%, *α* = 0.05). As TCP is already used for a long time in practice in several centers, the Bayesian design is preferable for ethical reasons (less patients to include), for economical ones and for feasibility (centers could be reluctant to include too many patients).

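### The half-mean 'pessimistic' prior still gives TCP an 88% prior chance of benefit, so agreement with it is no evidence of robustness

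*Protocol article*

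**What the plan says.** Section 2.6 (Sample size) gives the elicited opinions on the difference in remission percentage as "0%–10%: 1 expert; 10%–20%: 12 experts; 20%–30%: 4 experts; 30%–40%: 3 experts; 40%–50%: 0". It summarises them thus: "The mean (±SD) of this distribution is 0.195 (±0.0825"), which it says "corresponds an a priori of 23" virtual subjects per group.

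Section 3.1.1 (Primary objective) derives a second prior from the first: "A pessimistic a priori distribution was obtained from the experimental a priori distribution, dividing the mean of efficacy by 2 (keeping the same variance"). The decision on the treatment effect is then to be taken by looking at three distributions on the log odds ratio scale: the posterior under the elicited prior, the posterior under the pessimistic prior, and the observed data with an uninformative prior. "The 95% credible interval of efficacy will be estimated in these three situations". The section gives no numerical rule for success, and does not say how the three results are to be combined if they differ.

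**The concern.** A reader expects an analysis labelled pessimistic to make a favourable conclusion harder to reach. Halving a positive mean and keeping its SD does not do that here. The resulting prior still lies mostly on the side of benefit, and it adds precision to the data. Both features can bring the credible interval clear of zero sooner than the data would alone.

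The interpretation of the primary result is at stake. Two of the three distributions favour TCP and the third is flat, so none asks whether the result would persuade someone who doubts the therapy. If the elicited and pessimistic posteriors agree, the report could present this as a result that survives a cautious prior, when no cautious prior has been applied.

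**Working it through.** **Inputs from the article.** Elicited mean 0.195 and SD 0.0825 (2.6); mean halved, variance kept (3.1.1); 40 per arm (2.6).

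**Assumptions.** Control remission is not stated, so I use 20-50%. Success is taken as a 95% credible interval lying above no effect.

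**1. Reproducing the plan's figures.** Band midpoints 5, 15, 25 and 35 points, weighted 1, 12, 4 and 3, give mean 0.195 and SD 0.0826. Virtual n = 0.195 × 0.805 / 0.0825² = 23.06. Both agree with section 2.6.

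**2. The pessimistic prior.** Mean 0.195/2 = 0.0975, SD 0.0825. P(benefit) = Φ(0.0975/0.0825) = Φ(1.18) = 88.1%. The central 95% of the prior runs from -6.4 to +25.9 points. For the elicited prior, P(benefit) = 99.1%. Converting to the log odds ratio by the delta method gives 86-92% for the pessimistic prior at control rates of 20-50%.

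**3. Observed difference needed.** With prior mean m, prior SD t and data standard error s, the lower 95% limit exceeds zero when d > s² × [1.96 × √(1/t² + 1/s²) − m/t²]. Here 1/t² = 146.9 and m/t² = 14.32. With s = √(2p(1−p)/40):

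- p = 0.2: s = 0.0894 and 1/s² = 125. d > (1.96 × √271.9 − 14.32)/125 = 0.144. Data only: 1.96 × 0.0894 = 0.175.
- p = 0.5: s = 0.1118 and 1/s² = 80. d > (1.96 × √226.9 − 14.32)/80 = 0.190. Data only: 0.219.

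This s uses the control rate in both arms. With each arm's own observed rate, the comparison is:

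| Control rate | Pessimistic prior | Data only |
|---|---|---|
| 20% | 16.3 points | 19.6 points |
| 30% | 18.0 | 21.0 |
| 40% | 18.6 | 21.4 |
| 50% | 18.2 | 20.9 |

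The gap is about 3 points either way. Its direction does not depend on the assumed control rate: the pessimistic prior lowers the threshold whenever the data standard error is below 0.156, and with 40 per arm it cannot exceed √(2 × 0.25/40) = 0.112.

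**4. In patients.** With observed-rate standard errors on the risk-difference scale, the TCP remissions needed (pessimistic v data only) are 15 v 16 at 8/40 controls, 20 v 21 at 12/40, 24 v 25 at 16/40 and 28 v 29 at 20/40. The gap is two at 10/40 (17 v 19). On the log odds ratio scale it is one patient at 12/40, 16/40 and 20/40. At 8/40 the pessimistic prior needs 14, 15 or 16 against 17, depending on how the prior SD is converted.

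**5. False positives in TCP's favour, deciding on this posterior alone.** Exact binomial enumeration on the risk-difference scale at 20-50% gives 4.7-6.0%, against 2.6-2.8% for data only. The upper end depends on whether the standard error uses raw or half-count-adjusted rates; with the adjustment it is 5.4%. Log odds ratio conversions give mostly 4.3-6.0% against 2.0-2.8%. The lowest is 3.0%, against 2.8% for data only, in one conversion at a control rate of 50%.

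**6. If no difference is observed.** Posterior mean/SD = 14.32/√(1/t² + 1/s²), which is 14.32/16.49 = 0.87 at p = 0.2 and 14.32/15.06 = 0.95 at p = 0.5. The probability that TCP is better is therefore 81-83%.

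**The case against.** The strongest reply is that the safeguard is already planned. The data-only analysis is one of the three, with its own interval and the usual error rate of about 2.5% in one direction. If all three must agree, the data-only analysis is the binding one and the pessimistic prior cannot loosen the decision. This stands as a limit on the harm. It also shows the weakness of the label: on the risk-difference scale, every outcome with 40 per arm that succeeds on data only also succeeds under the pessimistic prior, so the latter adds no hurdle.

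The construction is also openly stated, and the word is fair relative to an elicited prior for which experts had already been asked to be as pessimistic as possible. The discussion section concedes that a prior resting on opinion is a limitation. The article never calls this prior sceptical or a robustness check. All of that stands, and the article makes no false statement here.

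A reader might go further and infer that the trial's own error rate is inflated to 5-6%, or that success comes three patients sooner. The article does not support either inference. It proposes no decision on this posterior alone and states no rule, and the three-patient gap (14 v 17) is the extreme of the log odds ratio conversions.

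The size also depends on the stated SD. If it were re-read as the SD of a difference between two groups of 23, P(benefit) would be about 75-80% and the threshold at most about 1 point below data only. That is not the variance given, and the prior would still favour TCP.

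**Conclusion.** The point holds in a bounded form. The 88% follows from the article's own mean and SD, with no outside assumption beyond a normal prior on the risk-difference scale. The absence of any sceptical distribution among the three can be read directly from section 3.1.1. The lower threshold (about 3 points), the typical one-patient gap and the false-positive rate of roughly 4.5-6% against 2-3% are conditional on the assumed success rule and control rates. They describe this posterior taken alone, not the trial's overall decision. The practical consequence is for interpretation: agreement with the 'pessimistic' posterior should not count as support for the primary result beyond what the data-only analysis gives.

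**What to change.** In section 3.1.1, add a sceptical prior centred on no difference (log odds ratio 0), with its SD fixed before the data are seen. Report its posterior and 95% credible interval beside the other three. One convention leaves 5% probability above the elicited effect: SD = 0.195/1.645 = 0.119 on the risk-difference scale. Because the analysis is on the log odds ratio scale, state the SD on that scale too, with the control remission rate used to convert it. Other SDs are defensible, and this one need not be the sole condition for claiming robustness. Rename the half-mean prior 'attenuated', keep it as a descriptive analysis, and do not cite it as cautious or as a robustness check.

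The cost is a change of wording and one more posterior from the same data, with no extra patients. The added posterior will be less favourable: with SD 0.119 it needs about 22-30 observed points at control rates of 20-50% (step 3 formula with m = 0, control-rate standard error), for example 1.96 × √(71.2 + 125)/125 = 0.22 at 20%.

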### Population and sampling

2.1

Participants are recruited in six outpatient hospitals and psychological care centers in France in which every main therapist providing TCP has followed the same training. The study involves first and second generation of migrant children and adolescents suffering from depression resistant to a first‐line therapy, their families, and the therapists. The recruitment is planned to be from January 2020 to July 2022.

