### Randomization

2.3

Participants are randomized with a 1:1 allocation ratio to “usual care and waiting list for TCP for at least 34 weeks” (control group) or “usual care and TCP beginning in the 6 following weeks” (experimental group). Every participant continues his/her usual treatment with the first‐line medical team throughout the duration of the study. As it is a pragmatic real‐life study, usual treatment may vary from one patient to another and from one first‐line medical team to another. It may include psychotherapy (individual, in group, or family therapy), medications, or institutional care (day‐hospital or inpatient care).

The randomization is centralized, stratified according to the recruitment center, with an unknown block size except from the statistician of the research center unit who generated this allocation sequence independently from the investigators and the statistician of the study. The allocation sequence was prepared using NQuery Advisor^®^ v7.0, validated software using pseudorandom numbers generator, and the randomization is performed electronically (IWRS) using the Cleanweb application (Télémédecine) software.

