### Quantitative analysis

3.1

Analyses will be performed according to the intention to treat (ITT) principle and no interim analysis will be performed. For the primary objective, as the iCGI severity score ≥4 is an inclusion criterion, all patients will have at least a measure at W0 and will be included in the ITT analysis. For patients with missing data on the iCGI assessment at W34, in case of less than 5% of missing data, the last observation carried forward will be used as imputation method, multiple imputations will be used otherwise (Jakobsen, Gluud, Wetterslev, & Winkel, 2017). For the secondary objectives, as mixed models will be used, missing data will not be imputed. For every objective, per protocol analyses will be performed as sensitivity analyses. The per protocol population is defined as patients for who the baseline and the last planned measure (W34) of the considered endpoint are available and who received the allocated intervention assigned by the randomization.

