#### Secondary objectives

3.1.2

They will be analyzed using a frequentist perspective, but they will be considered as exploratory in nature. For this reason, no adjustment for multiple testing will be done. Score (iCGI, CDRS‐R, and STAIC‐State) change from baseline to W34 will be analyzed using a mixed‐effects model for repeated measures with treatment group, visit, and treatment group‐by‐visit interaction as fixed effects and the baseline score and center as covariates. The persistence of the efficacy of TCP over time will be evaluated using paired Student's *t*‐test comparing the mean of the score (iCGI, CDRS‐R, and STAI‐C‐State) at W34 and W52 in the experimental group.

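### LOCF for missing week-34 iCGI when under 5% are missing is an avoidable weakness of small effect; secondarily, the article names no covariate for the primary effect

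*Protocol article*

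**What the plan says.** **Missing week-34 (W34) scores.** Section 3.1 (Quantitative analysis) keeps every randomised patient in the primary analysis, because the entry criterion guarantees an iCGI score at W0. For a missing W34 score the rule is: "in case of less than 5% of missing data, the last observation carried forward will be used as imputation method", with multiple imputation in all other cases. Remission (section 2.4.1) means that three blinded experts' ratings of the W34 film average below 4. Entry (section 2.1.1) requires a score of at least 4. Table 2 schedules the iCGI at W0, W6, W13, W20, W27 and W34.

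**Primary effect.** Section 3.1.1 combines a normal distribution for the observed log odds ratio with an elicited prior and with a pessimistic prior. The third reading is taken "from the distribution of observed data (uninformative prior"). No covariate is named for any of the three.

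**Design and secondary models.** Section 2.3 states: "The randomization is centralized, stratified according to the recruitment center". Section 2.1 gives six centres and section 2.6 gives "40 in experimental group and 40 in control group". The exploratory mixed models in section 3.1.2 include "the baseline score and center as covariates".

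**The concern.** LOCF has three weaknesses here.

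- It assumes that a patient under treatment does not change after the last visit attended.
- A patient with only the W0 score must be counted as not remitted, because entry required 4 or more and remission requires less than 4. A patient last seen between W6 and W27 is frozen at that visit, so the direction of the error is not fixed.
- It is a single imputation, so the credible interval treats the filled value as if it had been observed.

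The choice of method also turns on one patient at the threshold. None of this buys anything, because multiple imputation is already in the plan and up to five earlier iCGI scores are available as predictors.

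The second matter is precision. With 40 patients per group, a primary effect estimated without the stratification factor and baseline severity may give wider intervals than necessary. As the article reads, the exploratory models are specified more fully on this point than the analysis that decides the trial.

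**Working it through.** **The plan's own figures.** The 23 virtual subjects reproduce: 0.195 × 0.805 / 0.0825² = 23.06. Adding 40 gives 63 per group. The control remission rate is not stated. At an assumed 20% against 43%, two-sided 5% and 80% power, with pooled variance and no continuity correction, the required size is 63 per group (power 0.801). Over control rates of 5% to 50% it runs from 40 to 73. On the same formula and the 20% control rate, the 40 real patients per group alone give power of 0.604 for 23 points and 0.479 for the prior mean of 19.5 points. The reading without a prior therefore has little precision to spare.

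**How many patients LOCF can touch.** 3/80 = 3.75%, below 5%, so LOCF applies. 4/80 = 5%, not below 5%, so multiple imputation applies. The maximum is three patients.

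**Size of the LOCF error**, with 40 per group:

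- Bound: 3/40 = 0.075, reached for example when all three are in one group and all are misclassified in the same direction.
- Expected bias if the three would have remitted with probability *q* and LOCF sets all to non-remission: 3*q*/40 if all are in one group; (2*q* − *q*)/40 = *q*/40 if they split 2:1. For *q* = 0.2 to 0.4 (assumed) this is 0.015 to 0.030, or 0.005 to 0.010.
- Standard error of the difference, √[p₁(1−p₁)/40 + p₂(1−p₂)/40]: 0.100 for 20% against 39.5%, 0.107 for 30% against 49.5%, 0.110 for 40% against 59.5%. The bound is thus about 0.7 standard errors and the expected bias at most about 0.3 (0.030/0.100).

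**What adjustment could gain.** The article gives neither a baseline–outcome association nor a centre effect, so both are assumed and varied. Simulation: 80 patients, six centres of unequal size, allocation balanced within centre, control remission about 30%, true difference about 0.19 to 0.20, 1,500 runs per scenario. The adjusted logistic model had baseline and centre, with the four smallest centres merged. The variance ratio is for the difference standardised to the marginal scale; the rejection rate is for the treatment coefficient at 5%.

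| Log-odds slope per baseline SD; centre SD | Variance ratio, adjusted/unadjusted | Rejection rate, unadjusted → adjusted |
|---|---|---|
| 0; 0 | 1.015 | 0.460 → 0.464 |
| 0.5; 0.3 | 0.999 | 0.431 → 0.453 |
| 0.8; 0.5 | 0.887 | 0.435 → 0.486 |
| 1.2; 0.7 | 0.802 | 0.436 → 0.527 |

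With no treatment effect, rejection was 0.055 unadjusted and 0.058 adjusted in the first scenario, and 0.048 and 0.045 in the third. A variance ratio of 0.80 is worth 40/0.80 = 50 patients per group in place of 40. These are frequentist tests of the data alone, so they bear most directly on the reading without a prior. Where a prior carries part of the weight, the gain in the posterior is smaller.

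**The case against.** **On LOCF.** The threshold is fixed in advance and depends on how much is missing, not on outcomes or on the treatment effect, so it is not an open choice made after seeing results. It reaches three patients at most. The per-protocol sensitivity analysis requires a W34 measurement, so no carried-forward value enters it. All of this stands and is why the effect is small. But the per-protocol set also drops patients who did not receive their allocated intervention, so it does not isolate the effect of LOCF.

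A reader might also infer that LOCF always puts a different kind of rating into the endpoint. The entry score must exist before randomisation, so it cannot be the panel rating made after follow-up ends. For W6 to W27, however, section 2.5.3 repeats the baseline assessment process, which is filmed. Those films could be rated by the same experts, and the article does not say otherwise.

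**On covariates.** A reader might infer that the primary analysis is crude and ignores the strata. The article does not say so. The words about observed data separate the reading without a prior from the two with one; they say nothing about adjustment. A log odds ratio and its variance can come from an adjusted model, and the covariates may be set out in the full protocol or analysis plan, which are not at hand. Entry at 4 or above also restricts the baseline range and may weaken its association with outcome. These objections stand. What remains is the contrast with section 3.1.2, which names both covariates in an article that otherwise describes the primary model in some detail.

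**Conclusion.** The LOCF branch is stated outright and should go. Its plausible expected bias is about 0.5 to 3 percentage points, assuming three missing patients who would have remitted at 20% to 40% and are all carried forward as not remitted. The 7.5-point bound needs every error to push the difference the same way and should not be read as the likely effect.

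The covariate point is secondary and held with moderate confidence. It is a conditional request, not a finding that the analysis is unadjusted. Nor would leaving out centre or baseline bias the randomised comparison; the cost is precision, with intervals that tend to be too wide. The possible gain runs from nil to about 20% of variance, or 0 to about 9 points of power, and rests wholly on assumed associations.

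**What to change.** 1. Delete the LOCF branch. Use multiple imputation for missing W34 iCGI whatever the amount missing, with treatment group, centre and the W0 to W27 iCGI scores in the imputation model. Pool the effect and its variance over imputations before forming the three posteriors. The method is already planned, so the cost is a change of wording.

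2. Unless the full plan already does so, state that the primary effect is adjusted for centre (pooling small centres) and baseline iCGI, and standardise it to the marginal effect before combining it in all three posteriors. Standardisation matters because the prior was elicited on the difference in remission percentages, which is marginal, whereas an adjusted log odds ratio is conditional and not the same quantity. Data and prior must then be expressed on one scale. If the log odds ratio is kept, the standardised effect can be given as a marginal log odds ratio; a move to the risk difference would change the scale of all three posteriors and should be justified. The cost is a few degrees of freedom and a rule for pooling small centres, fixed before the films are rated.
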